#### **9.2.1.5 Sensitivity Analysis of Primary Endpoint**

The analyses for the primary endpoint for the pooled analysis will be repeated for participants who received two SDs of vaccine and the second dose is SD based on randomized treatment (ie, SDSD + LDSD Seronegative ITT for Efficacy analysis set).

### **9.2.2 Secondary Efficacy Analyses**

#### **9.2.2.1 Incidence of Asymptomatic SARS-CoV-2 Infection COV002 only**

The analysis for those endpoints will be conducted in a similar manner as described in Section 9.2.1.1 (see Pooled Analysis of Primary Efficacy Endpoint) but remove Study code from model.

#### **9.2.2.2 Duration of Follow-up since the Second Vaccination**

Summary by treatment group will be calculated for this variable.

### **9.2.2.3 Other Secondary Efficacy Endpoints**

The remaining endpoints will be analysed in the same manner as the pooled analysis of the primary efficacy endpoint as described in Section 9.2.1.1 (see Pooled Analysis of Primary Efficacy Endpoint). VE will not be computed unless 5 cases have accrued for the respective endpoint, but the distribution by groups will be presented.

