## 4.1 Planned Analyses

The proposed primary and interim pooled analyses provide an opportunity to produce early and robust estimates of efficacy to support rapid decision making in the present conditions of

this public health emergency. One interim analysis and one primary analysis are planned as below:

The interim analysis will be triggered when 53 COVID-19 cases (SARS-CoV-2 virologically confirmed) that occurred  $\geq 15$  days post the second dose have been reported in participants who received SD/SD (as defined in [Table 4](#)) across the AZD1222 and control groups in pooled studies. This would provide 77% power for the 20% threshold to assume a true vaccine efficacy of 70%. The analysis will include participants who received two doses, with a SD as the second dose (ie, participants who received LD/SD or SD/SD). For an individual study to be included in the pooled analysis of efficacy, a minimum of 5 primary endpoint defined cases must be accrued. For COV002, only cases accruing in efficacy study groups will be included (groups 4, 6, 9, 10).

The primary analysis will be triggered when 105 COVID-19 cases (SARS-CoV-2 virologically confirmed) that occurred  $\geq 15$  days post the second dose have been reported in participants who received SD/SD (as defined in [Table 4](#)) across the AZD1222 and control groups. This would provide 90% power for the 20% threshold to assume a true vaccine efficacy of 60%. The analysis will include participants who received two doses, with the second dose being SD (ie, participants who received LD/SD or SD/SD). For an individual study to be included in the pooled analysis of efficacy, a minimum of 5 primary endpoint defined cases must be accrued. For COV002, only cases accruing in efficacy study groups will be included (groups 4, 6, 9, 10).

Gamma Alpha-Spending function is used to control the overall Type 1 Error at 5%. The planned alpha level is 1.13% for interim analysis and 4.44% for primary analysis. The minimum observed VE if an interim or primary analysis demonstrates evidence of efficacy is 64% and 48%, respectively.

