## 7. OVERVIEW OF ANALYSIS CONVENTIONS

### 7.1 Data Presentation

The planned 5% alpha will be split across the interim and primary analyses as described in Section 4.1. All efficacy analyses will use a 2-sided alpha test unless otherwise stated. P values will be rounded to 4 decimal places. If a p value is less than 0.0001, it will be reported as “< 0.0001”. If a p value is greater than 0.9999, it will be reported as “> 0.9999”.

All continuous variables will be summarized using descriptive statistics, reporting N, mean, standard deviation, median, minimum, and maximum. As appropriate, minima and maxima will be reported with the same precision as the raw values; medians and means will have one additional decimal place; standard deviation will have 2 additional decimal places. Data will be displayed by treatment group in all listings, as needed. Participants will be uniquely identified in the listings by the combination of study number, study site number, and subject number.

For discrete, or categorical data, percentages will be suppressed when the count is zero. A row denoted as “Missing” will be included in the count tabulations where necessary to account for dropouts or missing values.

All regulatory analyses will be performed using SAS®, Version 9.4 or higher (SAS Institute Inc., Cary, NC).

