## 9.2.1 Primary Efficacy Analyses

### 9.2.1.1 Pooled Analysis of Primary Efficacy Endpoint

A Poisson regression model with robust variance (Zou 2004) will be used as the primary efficacy analysis model to estimate the relative risk (RR) of the incidence of SARS-CoV-2 virologically-confirmed primary symptomatic COVID-19 between the AZD1222 and control groups. The model contains the term of study code, treatment group, and age group at randomization (ie, 18-55 years, 56-69 years, and  $\geq 70$  years). The logarithm of the period at risk for primary endpoint for pooled analysis will be used as an offset variable in the model to adjust for volunteers having different follow up times during which the events occur.

Vaccine efficacy (VE), which is the incidence of infection in the vaccine group relative to the incidence of infection in the control group expressed as a percentage, will be calculated as  $VE = 1 - \text{relative risk}$ . The VE, and its corresponding 2-sided  $(1-\alpha)$  % confidence interval (CI), will be estimated from the model. In addition, the 2-sided p value testing null hypothesis that the incidence of SARS-CoV-2 virologically-confirmed primary symptomatic COVID-19 between AZD1222 and control groups are the same will be obtained from the model. Statistical significance will be achieved if the 2-sided p value is  $\leq \alpha$ , where  $\alpha$  for interim and primary analysis as described in Section 4.1.

The Poisson regression with robust variance analysis will be implemented by using the SAS PROC GENMOD procedure for binary data with the REPEATED statement for subject ID and logarithm link. The estimated parameter  $\hat{\beta}$  [ie,  $\log(\widehat{RR})$ ], 2-sided  $(1-\alpha)$  % CI for  $\hat{\beta}$ , and the 2-sided p value will be obtained from the SAS outputs. The estimated RR and corresponding CI for the RR is given by exponentiating  $\hat{\beta}$  and its confidence limits. Therefore, the percent of VE is given by  $[(1 - \exp(\hat{\beta})) * 100\%]$ . The CI for the percent of VE is given by  $[(1 - \exp(\text{upper confidence limit for } \hat{\beta})) * 100\%, [1 - \exp(\text{lower confidence limit for } \hat{\beta})) * 100\%]$ .

If the Poisson regression model with robust variance fails to converge, the exact conditional method for stratified Poisson regression using PROC GENMOD with the exact statement will be used.

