#### **9.2.1.2 Secondary Analysis of Primary Endpoint**

The analyses for the primary endpoint for the pooled analysis will be repeated for participants who received two SDs of vaccine (ie, SDSD Seronegative for Efficacy analysis set).

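### The primary's significance rule is carried by cross-reference to the SD/SD repeat and 16 secondary incidence endpoints without a gate, order or descriptive label, so the 5% overall error does not cover them

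*SAP*

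**What the plan says.** Section 4.1 plans an interim and a primary analysis, triggered by 53 and 105 cases, and sets the overall type I error at 5% by gamma alpha spending: "The planned alpha level is 1.13% for interim analysis and 4.44% for primary analysis".

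Section 9.2.1.1 describes the Poisson model, the VE and its confidence interval, the p value and the decision rule together. The rule begins "Statistical significance will be achieved if the 2-sided p value is" and goes on to require a value at or below the alpha of 4.1. Section 7.1 adds: "All efficacy analyses will use a 2-sided alpha test unless otherwise stated".

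Three later sections refer back to this procedure:

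- 9.2.1.2, the SD/SD set: "The analyses for the primary endpoint for the pooled analysis will be repeated for participants who received two SDs of vaccine".
- 9.2.2.1, the two asymptomatic-infection endpoints: "The analysis for those endpoints will be conducted in a similar manner as described in Section 9.2.1.1", without the study term.
- 9.2.2.3, the other fourteen incidence endpoints: "The remaining endpoints will be analysed in the same manner as the pooled analysis of the primary efficacy endpoint as described in Section 9.2.1.1".

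The only condition attached is in 9.2.2.3: VE is not computed below five cases. Two secondary items are summarised without a test, namely duration of follow-up (9.1.2.8, 9.2.2.2) and nucleocapsid antibody (9.1.2.18, 9.2.2.4). Subgroups are introduced as exploratory in 7.2. The phrase Multiple Testing Procedure occurs only as a category name under the amendment history.

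**The concern.** The alpha split is built for one contrast, the primary endpoint in the SDSD + LDSD Seronegative set. The cross-references pass on the whole of 9.2.1.1, and nothing in them leaves the decision rule behind. Read as written, the SD/SD repeat and each secondary incidence endpoint can be called statistically significant at the full alpha of either look, even when the primary test has failed.

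This matters because the SAP supports a marketing authorisation application. Severe COVID-19 is the only secondary efficacy objective in 2.2, and SD/SD cases trigger both analyses, so both are natural candidates for a claim. A reader who sees 5% overall error in 4.1 and a significance statement for severe disease could take the first to cover the second. It does not.

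**Working it through.** **Step 1. Reproduce the plan's error rate for the primary test.** The information fraction is t = 53/105 = 0.505. The SAP gives no gamma parameter; −2.5, found by trial, matches its figures. Gamma spending at the interim is

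0.05 × (1 − e^(2.5 × 0.505)) / (1 − e^(2.5)) = 0.0113,

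which is the stated 1.13%. The two test statistics have correlation √0.505 = 0.710. With two-sided limits of 2.533 (1.13%) and 2.010 (4.44%), the bivariate normal probability of crossing at either look is 0.04997. The stated 5% is therefore correct for one test, or 2.5% in the direction of efficacy.

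**Step 2. Count the tests that inherit the rule.** Sections 9.1.2.1 to 9.1.2.7 give 7 incidence endpoints and 9.1.2.9 to 9.1.2.17 give 9, so 7 + 9 = 16. Two of these fall under 9.2.2.1 and fourteen under 9.2.2.3. The SD/SD repeat of the primary is one more. Duration of follow-up and nucleocapsid antibody are not counted because no test is planned for them.

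**Step 3. Chance of at least one false rejection at the primary analysis alone.** For m independent null tests at two-sided 4.44% the chance is 1 − (1 − 0.0444)^m. In the direction of efficacy each test has 0.0444/2 = 0.0222, giving 1 − (1 − 0.0222)^m.

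- m = 16: 1 − 0.9556^16 = 0.52 two-sided; 1 − 0.9778^16 = 0.30 for efficacy.
- m = 8: 1 − 0.9556^8 = 0.30 two-sided; 1 − 0.9778^8 = 0.16 for efficacy.

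The endpoints are nested, so independence is an upper bound. With a common correlation ρ and limit c = 2.010, the two-sided chance is

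1 − ∫ [Φ((c − √ρ u)/√(1 − ρ)) − Φ((−c − √ρ u)/√(1 − ρ))]^m φ(u) du,

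and the efficacy figure drops the second Φ term. The SAP gives no correlations; these are assumptions.

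| Null tests | ρ = 0 | ρ = 0.5 | ρ = 0.9 |
|---|---|---|---|
| 16, two-sided | 52% | 34% | 13% |
| 16, efficacy direction | 30% | 17% | 7% |
| 8, two-sided | 30% | 23% | 11% |
| 8, efficacy direction | 16% | 11% | 5% |

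The rows for 8 illustrate rare endpoints missing the five-case minimum; the SAP does not say how many will.

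**Step 4. The primary and its SD/SD repeat only.** Table A1 gives about 15600 SD/SD participants among about 19000. Taking the null correlation as √(15600/19000) = 0.91, the chance that at least one of the two tests rejects at the primary analysis is 6.2% two-sided, against 4.44% for one test.

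**Step 5. Both looks.** If each endpoint had the primary's information fraction, the 17 non-primary tests (16 plus SD/SD) would give a two-sided chance over the two looks of 58%, 39% and 15% at ρ = 0, 0.5 and 0.9.

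**The case against.** The strongest reply is that only the model was meant to carry over. The null hypothesis in 9.2.1.1 names the primary endpoint, the alpha in 4.1 is tied to primary case counts, 9.2.2.3 speaks of when VE is computed and not of significance, and 7.1 may only fix sidedness. Nowhere does the SAP say that the 5% covers secondary endpoints. That reading is possible, and it shows that the wording is ambiguous. It does not remove the point, because 9.2.1.1 holds model, interval and decision rule together, no cross-reference separates them, and the plan uses summary or exploratory wording elsewhere when no formal test is intended.

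Three further replies stand in part.

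- **Number of tests.** A reader might count the whole Table A1 grid, which has 5 + 6 + 6 + 5 = 22 non-primary combinations. The any-dose row, however, appears to be the one that a table footnote marks as required for safety evaluation (the footnote letters are shifted). The count of 16 from 9.1.2 includes five endpoints measured from the first dose; without them 11 remain, between the two cases in the table.
- **Direction.** A reader might take the two-sided figures as chances of a false efficacy claim. Half of those rejections favour control, so the efficacy figures are about half as large.
- **Correlation.** The analysis sets overlap heavily. At 0.9 the efficacy figures fall to 5% to 7%, which is still at least twice 2.5%.

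**Conclusion.** The concern holds for the SD/SD repeat and the 16 secondary incidence endpoints. As written, they share the primary's significance rule at full alpha, with no gate, order or descriptive label, and the 5% of 4.1 does not cover them. At the primary analysis, 16 null tests carry a 13% to 52% chance of some two-sided rejection and a 7% to 30% chance of a false result for efficacy. With 8 tests these are 11% to 30% and 5% to 16%. The sizes rest on assumed common correlations of 0 to 0.9, no true effect on any endpoint, and an unknown number of endpoints reaching five cases. The direction does not depend on these choices: adding tests at the same level raises the error unless they are perfectly correlated.

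Two stronger inferences are not supported. The primary test's own error is not inflated: it reproduces as 4.997%, and no estimate or case trigger is affected. Nor does every secondary efficacy endpoint inherit the rule, since duration of follow-up and nucleocapsid antibody are summary only. The plan should be changed before results are described as significant, but the primary conclusion does not depend on it.

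**What to change.** In 9.2.1.1, limit the sentence defining statistical significance to the primary endpoint in the SDSD + LDSD Seronegative for Efficacy set. In 9.2.1.2, 9.2.2.1 and 9.2.2.3, state that all other efficacy analyses, including the first-dose and any-dose windows, are descriptive, with nominal confidence intervals and p values and no claim of significance. Amend 7.1 to match.

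If the sponsor wants a confirmatory claim for SD/SD or severe COVID-19, it should be tested only after the primary has crossed its boundary, in an order fixed in advance and with its own valid boundary over the two looks. The order is the sponsor's choice. For severe disease the boundary cannot simply be copied from 4.1, because spending by case fraction needs a planned number of severe cases and the SAP gives none.

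The descriptive option costs only wording; data, estimates and case triggers stay as they are. A confirmatory sequence also needs those boundaries worked out. The downside is that endpoints outside the sequence, or after a failed step in it, can no longer be called statistically significant.

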### **9.2.2.4 Secondary Efficacy Analyses for Endpoints Based on Nucleocapsid: Detection Antibody SARS-CoV-2 Nucleocapsid Related Endpoints**

Percentage of participants positive for SARS-CoV-2 nucleocapsid antibody levels over time will be summarized overall and by baseline seropositivity status. At each time point the % positive for nucleocapsid antibody will be summarized for those who were not previously positive at any time point and in those who were previously positive at least one time point.

## **10. SAFETY ANALYSIS**

Safety summaries described below will be performed by treatment group (AZD1222 and Control) for analysis sets planned in [Table A2](#).

### **10.1 Adverse Events**

#### **10.1.1 Reporting of Adverse events**

All local and systemic AEs that occur within 28 days after each vaccination observed by the Investigator or reported by the participant, will be recorded by the participants in the Diary of Symptoms and by the Investigators in the study CRF. For COV001, diary cards for the second vaccines will not be filled out for participants in groups 2f, 2g, 4c and 4d. For COV002, solicited and unsolicited AEs will be reported for 7 days only for group 1-3, 5, 7, 8, 11 and 12 and a subset of up to 3000 participants for groups 4, 6, 9, and 10. In COV003, solicited AEs will be reported for a subset of 200 participants.

SAEs and Adverse Events of Special Interest will be collected throughout the study period.

Adverse events will be coded using the Medical Dictionary for Regulatory Activities (MedDRA) Version 23 or higher.

#### **10.1.2 Evaluation of Severity**

The severity of AEs will be assessed according to toxicity rating scales adapted from the FDA for healthy volunteers recruited in preventive vaccine clinical trials, listed in the specific study work instructions and [Table 7](#). For COV005, DAIDS grading the severity of adult and paediatric adverse events is used. For solicited AE, refer to [Appendix B](#).

**Table 7**                      **Severity Rating Criteria for Physical Observations (Applies to Adults Only) for COV001, COV002 and COV003**

| Vital Signs                       | Grade 1
(mild) | Grade 2
(moderate) | Grade 3
(serious) | Grade 4
Potentially fatal                    |
|------------------------------------------|---------------------------|-------------------------------|------------------------------|---------------------------------------------------------|
| Fever (oral)                             | 38, 0°C- 38, 4°C          | 38.5°C - 38.9°C               | 39.0°C - 40°C                | > 40°C                                                  |
| Tachycardia (bpm) a           | 101 – 115                 | 116-130                       | > 130                        | A/E visit or hospitalization for arrhythmia             |
| Bradycardia (bpm) b           | 50 – 54                   | 45 – 49                       | < 45                         | A/E visit or hospitalization for arrhythmia             |
| Systolic hypertension (mmHg)             | 141 -150                  | 151 – 155                     | ≥ 155                        | A/E visit or hospitalization for malignant hypertension |
| Diastolic hypertension (mmHg)            | 91 – 95                   | 96 – 100                      | > 1100                       | A/E visit or hospitalization for malignant hypertension |
| Systolic hypotension (mmHg) c | 85 – 89                   | 80 – 84                       | < 80                         | A/E visit or hospitalization for hypotensive shock      |
| Respiratory Rate - breaths per minute    | 17 – 20                   | 21-25                         | > 25                         | Intubation                                              |

a Measured after ≥10 minutes at rest

b When the resting heart rate is between 60 to 100 beats per minute. Use the clinical criterion when characterizing bradycardia among some populations of healthy participants, for example, conditioned athletes.

c Only if symptomatic (for example, dizziness/vertigo)

A/E = accident & emergency department.

**Table 8**                      **Severity Grading Criteria for Select Physical Observations (Based on DAIDS Grading Table; Version 2.1 – July 2017 for COV005)**

| Vital signs | Grade 1
(mild)                                                                                                  | Grade 2
(moderate)                                                                                                     | Grade 3
(severe)                                                                                                      | Grade 4
Potentially life threatening                                                                                                                                           |
|--------------------|----------------------------------------------------------------------------------------------------------------------------|-----------------------------------------------------------------------------------------------------------------------------------|----------------------------------------------------------------------------------------------------------------------------------|-------------------------------------------------------------------------------------------------------------------------------------------------------------------------------------------|
|                    | Mild symptoms causing no or minimal interference with usual social & functional activities with intervention not indicated | Moderate symptoms causing greater than minimal interference with usual social & functional activities with intervention indicated | Severe symptoms causing inability to perform usual social & functional activities with intervention or hospitalization indicated | Potentially life-threatening symptoms causing inability to perform basic self-care functions with intervention indicated to prevent permanent impairment, persistent disability, or death |

**Table 8**                      **Severity Grading Criteria for Select Physical Observations (Based on DAIDS Grading Table; Version 2.1 – July 2017 for COV005)**

| Vital signs                           | Grade 1
(mild)                                                                                | Grade 2
(moderate)                                                                                   | Grade 3
(severe)                                                                   | Grade 4
Potentially life threatening                                                                                                                                              |
|----------------------------------------------|----------------------------------------------------------------------------------------------------------|-----------------------------------------------------------------------------------------------------------------|-----------------------------------------------------------------------------------------------|----------------------------------------------------------------------------------------------------------------------------------------------------------------------------------------------|
| Arthralgia                                   | Joint pain causing no or minimal interference with usual social & functional activities                  | Joint pain causing greater than minimal interference with usual social & functional activities                  | Joint pain causing inability to perform usual social & functional activities                  | Disabling joint pain causing inability to perform basic self-care functions                                                                                                                  |
| Arthritis                                    | Stiffness or joint swelling causing no or minimal interference with usual social & functional activities | Stiffness or joint swelling causing greater than minimal interference with usual social & functional activities | Stiffness or joint swelling causing inability to perform usual social & functional activities | Disabling joint stiffness or swelling causing inability to perform basic self-care functions                                                                                                 |
| Chills                                       | Symptoms causing no or minimal interference with usual social & functional activities                    | Symptoms causing greater than minimal interference with usual social & functional activities                    | Symptoms causing inability to perform usual social & functional activities                    | NA                                                                                                                                                                                           |
| Fatigue or Malaise
Report only one | Symptoms causing no or minimal interference with usual social & functional activities                    | Symptoms causing greater than minimal interference with usual social & functional activities                    | Symptoms causing inability to perform usual social & functional activities                    | Incapacitating symptoms of fatigue or malaise causing inability to perform basic self-care functions                                                                                         |
| Fever (non-axillary temperatures only)       | 38.0 to < 38.6°C                                                                                         | ≥ 38.6 to < 39.3°C                                                                                              | ≥ 39.3 to < 40.0°C                                                                            | ≥ 40.0°C or ≥ 104.0°F                                                                                                                                                                        |
| Headache                                     | Symptoms causing no or minimal interference with usual social & functional activities                    | Symptoms causing greater than minimal interference with usual social & functional activities                    | Symptoms causing inability to perform usual social & functional activities                    | Symptoms causing inability to perform basic self-care functions OR Hospitalization indicated OR Headache with significant impairment of alertness or other neurologic function |

**Table 8**                      **Severity Grading Criteria for Select Physical Observations (Based on DAIDS Grading Table; Version 2.1 – July 2017 for COV005)**

| Vital signs                                                                                                                    | Grade 1
(mild)                                                                | Grade 2
(moderate)                                                                            | Grade 3
(severe)                                                                                    | Grade 4
Potentially life
threatening                                                                                                        |
|---------------------------------------------------------------------------------------------------------------------------------------|------------------------------------------------------------------------------------------|----------------------------------------------------------------------------------------------------------|----------------------------------------------------------------------------------------------------------------|------------------------------------------------------------------------------------------------------------------------------------------------------------|
| Myalgia
(generalized)                                                                                                              | Muscle pain causing no or minimal interference with usual social & functional activities | Muscle pain causing greater than minimal interference with usual social & functional activities          | Muscle pain causing inability to perform usual social & functional activities                                  | Disabling muscle pain causing inability to perform basic self-care functions                                                                               |
| Pain (not associated with study agent injections and not specified elsewhere)
Specify location                              | Pain causing no or minimal interference with usual social & functional activities        | Pain causing greater than minimal interference with usual social & functional activities                 | Pain causing inability to perform usual social & functional activities                                         | Disabling pain causing inability to perform basic self-care functions OR Hospitalization indicated                                                  |
| Acute Allergic Reaction                                                                                                               | Localized urticaria (wheals) with no medical intervention indicated                      | Localized urticaria with intervention indicated OR Mild angioedema with no intervention indicated | Generalized urticaria OR Angioedema with intervention indicated OR Symptoms of mild bronchospasm | Acute anaphylaxis OR Life-threatening bronchospasm OR Laryngeal edema                                                                        |
| Blood Pressure Abnormalities
Hypertension (with the lowest reading taken after repeat testing during a visit)
≥ 18 years of age | 140 to < 160 mmHg systolic OR 90 to < 100 mmHg diastolic                          | ≥ 160 to < 180 mmHg systolic OR ≥ 100 to < 110 mmHg diastolic                                     | ≥ 180 mmHg systolic OR ≥ 110 mmHg diastolic                                                             | Life-threatening consequences in a participant not previously diagnosed with hypertension (eg, malignant hypertension) OR Hospitalization indicated |
| Hypotension                                                                                                                    | No symptoms                                                                              | Symptoms corrected with oral fluid replacement                                                           | Symptoms AND IV fluids indicated                                                                        | Shock requiring use of vasopressors or mechanical assistance to maintain blood pressure                                                                    |

**Table 8                      Severity Grading Criteria for Select Physical Observations (Based on DAIDS Grading Table; Version 2.1 – July 2017 for COV005)**

| Vital signs                                              | Grade 1
(mild)                                                                                                                                               | Grade 2
(moderate)                                                                                                                                                                          | Grade 3
(severe)                                                                                      | Grade 4
Potentially life
threatening                                |
|-----------------------------------------------------------------|-------------------------------------------------------------------------------------------------------------------------------------------------------------------------|--------------------------------------------------------------------------------------------------------------------------------------------------------------------------------------------------------|------------------------------------------------------------------------------------------------------------------|------------------------------------------------------------------------------------|
| Dyspnea or
Respiratory
Distress
Report only one | Dyspnea on exertion with no or minimal interference with usual social & functional activities OR Wheezing OR Minimal increase in respiratory rate for age | Dyspnea on exertion causing greater than minimal interference with usual social & functional activities OR Nasal flaring OR Intercostal retractions OR Pulse oximetry 90 to < 95% | Dyspnea at rest causing inability to perform usual social & functional activities OR Pulse oximetry < 90% | Respiratory failure with ventilator support indicated (eg, CPAP, BPAP, intubation) |

